#### Exclusion criteria

Patients will be excluded from the study if: (1) they scored 20 or higher on the TIS which indicates normal truncal function [14]. Since patients should be able to improve their trunk performance by means of trunk rehabilitation, normal trunk performance should be excluded [14], (2) they scored lower than 2 on the Functional Ambulation Categories (FAC) as patients need to be able to ambulate without physical support to ensure that gait analysis can be executed safely, (3) they are not able to sit independently, without support and supervision, for 30 s on a stable surface. Patients will have to perform trunk exercises on unstable surfaces; therefore, a minimum truncal function is necessary to ensure a safe environment during training, (4) they suffer from other neurological and orthopedic disorders that could influence motor performance and balance, (5) they are unable to understand verbal instructions. The cognitive and communicative abilities of the patients will be assessed by a neuropsychologist or speech therapist of the rehabilitation hospital RevArte, and (6) they are patients over the age of 85 years because an hour of intense therapy will be too demanding for this population. Additionally, unpublished data from our research group suggest that involvement of the trunk during walking clearly changes after the age of 80 years. This decision was made to exclude gait patterns that resemble a geriatric gait pattern instead of a hemiplegic pattern. Although the patient population needed for this study is specific to patients who are able to walk and have an impaired truncal function, based on unpublished data, it is anticipated that approximately 35% of all hospitalized stroke patients will meet these criteria.

### Procedures

#### Recruitment and selection

The time schedule of enrollment, assessment, interventions, and follow-up according to the Standard Protocol Items: Recommendations for Interventional Trials (SPIRIT) guidelines can be found in Fig. 1. Patients are recruited and screened for eligibility in three consecutive steps. Firstly, the treating physiotherapists will be thoroughly briefed concerning the inclusion and exclusion criteria of the study since they will be providing the researchers with the information for possible inclusion. Next, study information will be given to potential participants by the main researcher. This comprises the objective and description of the study, the duration of the study, and its risks and benefits. If the patients are interested in the study, an appointment will be made to provide more detailed information and to answer possible questions. When the patient agrees to participate in the study, the informed consent will be signed before obtaining medical record admission to guarantee privacy. Lastly, after obtaining informed consent the patients will be screened by the primary investigator to assure inclusion by means of the TIS and the FAC. Information concerning stroke diagnosis, medical history, and stroke onset will be acquired from patient records.

**Fig. 1 Fig1:**
[figure not shown]
The schedule of enrollment, interventions, and assessments. Abbreviations: *wk* week, *wks* weeks, *yrs* years, *exp* experimental, *FAC* Functional Ambulation Categories, *TIS* Trunk Impairment Scale, *SS* single support, *DS* double support, *ROM* range of motion, *COM* center of mass

#### Baseline assessment

Clinical information comprises date of birth, type of stroke, location of stroke, medical history, drug therapy, and the use of orthosis and assistive devices. Both biomechanical and clinical assessment will be performed prior to intervention. The clinical assessment will consist of the following clinical tests: the Tinetti Test (TT); the Trunk Impairment Scale (TIS), Functional Ambulation Categories (FAC), and the Barthel Index (BI). The procedures of the clinical tests can be found in the studies of Tinetti et al. (1986), Verheyden et al. (2004), Holden et al. (1984), and Mahoney et al. (1965) [15–18]. The biomechanical assessment procedure will consist of a 3D, full body gait analysis which will be executed at the M^2^OCEAN movement analysis laboratory (Multidisciplinary Motor Centre Antwerp, University of Antwerp, Antwerp, Edegem). A VICON analysis system (VICON© Motion Systems Ltd., London, UK) with a measuring frequency of 100 Hz and a measurement error smaller than 1 mm and 1° will be used to measure kinematic parameters in all three planes; sagittal, frontal, and transversal. Eight infrared automated cameras (VICON T10 cameras, 100 fps, 1 Megapixel) will measure the 3D coordinates of the reflective markers. In addition, initial contact and toe off will be defined based on the ankle trajectories of the reflective markers together with 3 AMTI type OR 6-7 force plates (1000 fps, 46 × 50 × 8 cm) and one AccuGait® (1000 fps) force plate recording. The movement analysis laboratory is equipped with a 16-channel telemetric wireless surface electromyography (EMG) system (1080 Hz; Cometa, Rome, Italy) which measures muscle activity of the trunk and lower limb muscles. Recordings will be analyzed using the VICON Nexus 1.8.5. software and the Plug-In-Gait software package as clinical model. The joint rotation angles will be calculated from the YXZ Cardan angles derived by comparing the relative orientations of the two segments. For example, the knee angles will be calculated from the femur and the untorsioned tibial segments relative to the fixed laboratory axis. Subsequently, data will be reconstructed and the reflective markers will have to be labeled. After labeling, the data will be filtered to eliminate any recorded noise by means of a low-pass Butterworth filter (second order, zero phase, cutoff frequency 6 Hz). Furthermore, gait cycle events and parameters will be calculated from the filtered ankle marker trajectories. Data will be saved as c3d files and further processed in MATLAB® (The MathWorks, Inc., Natick, MA, USA) by means of customized MATLAB® scripts.

Gait analysis will commence by preparing the patient in a standardized manner. Firstly, the following anthropometrics will be determined to make an adequate 3D model of the patient: body height, body weight, leg length, shoulder width, thickness of the wrist and of the second metacarpophalangeal joint, distance between the medial and lateral humeral epicondyles, between the medial and lateral condyles of the femur, and between the medial and lateral malleoli. In addition, clinical assessment will be performed to assess the underlying problem of the abnormal gait pattern. A correctly executed clinical assessment is necessary to interpret the information provided by the full body gait analysis. The following characteristics will be assessed: (1) passive ROM of the hip, knee, ankle, and foot will be assessed by means of goniometry, (2) inspection of the foot (e.g., varus, valgus, claw toes, mid-foot break), (2) muscle length of the rectus femoris and hamstrings by means of the Duncan-Ely Test and the popliteal angle [19, 20], (3) muscle strength by means of manual muscle testing according to the guidelines of the Oxford Medical Research Council [21]. Isometric muscle force will be assessed during open-chain movements by providing manual resistance against these movements. The patient’s effort is graded on a scale of 0 to 5 of which 0 represents no observed movement and 5 represents normal muscle contraction against maximal resistance, (4) selectivity of movements is the ability to perform isolated joint movements without using flexor or extensor patterns or undesired movements at other joints. Selectivity of movements will be either normal, impaired, or unable, (5) muscle tone will be assessed by means of the Modified Tardieu Scale [22, 23]. This test quantifies spasticity by assessing the resistance to applied stretch at specified velocities. A score of 0 to 5 can be given implying no increase of resistance to rigid movement of the limb, respectively. In addition, the presence of clonus will be assessed, (5) sensitivity will be assessed by the revised Nottingham Sensory Assessment Scale [24]. Tactile sensation (light touch, pressure, and pin prick) and sharp-dull discrimination will be assessed at defined points of contact. Proprioception will be assessed to see if the patient is able to detect movement and in which direction, and (6) the Confusion Test, which assesses the selectivity of hip flexion movement and the force of the dorsal flexor muscles in a flexion synergy, will be performed [25].

Secondly, disposable gel electrodes (Kendall^TM^, 30 mm × 24 mm) will be applied after anthropometric measurements. Before application of the electrodes the skin will be properly prepared, by shaving and degreasing, to ensure a good electrode-skin contact and to minimize the risk of artefacts. Electrodes will be placed on the left and right musculus rectus femoris, musculus vastus lateralis, musculus biceps femoris, musculus semitendinosus, musculus tibialis anterior, musculus gastrocnemius and musculus erector spinae during maximal muscular contraction according to the SENIAM guidelines [26].

Thirdly, reflective markers will be placed on bony anatomical landmarks according to the standard Plug-In-Gait model combined with a more detailed spine model developed and assessed for reliability by Heyrman et al. (2013) [27]. These two models allow the computation of linear and angular displacements of the different body segments. Although, good intra-protocol repeatability has been established for the Plug-In-Gait model, variability due to differences in marker placement has shown to be the major contributor to overall variance [28, 29]. Therefore, a standardized protocol was implemented whereby bony landmarks were located by manual palpitation by the primary investigator. To diminish artefacts, the motion trackers were firmly affixed to the skin with double-sided tape. Reflective markers for the Plug-In-Gait model of the upper body are located at the front and back of the head (left and right), the processus spinosus (PS) of the seventh cervical vertebrae, the PS of the tenth thoracic vertebrae, the jugular notch of the sternum, the xiphoid process of the sternum, the left and right acromioclavicular joints, the left and right points of rotation of the elbow, the styloid process of the left and right ulna and radius, and on the dorsum of both hands just below the second metacarpals. Reflective markers for the Plug-In-Gait model of the lower body are located on the left and right spina iliaca anterior superior and spina iliaca posterior superior, the left and right points of knee rotation, the left and right lateral malleoli, the second left and right metatarsal heads, and the left and right calacanei. Reflective markers for the spine model are located on the PS of the second and sixth thoracic vertebrae, and the PS of the first, third, and fifth lumbar vertebrae. Four markers are attached at one third of the length of the femur and fibula in alignment with trochanter major, the rotation point of the knee, and the lateral malleolus to examine the presence of rotation in the lower limbs (Fig. 2).

**Fig. 2 Fig2:**
[figure not shown]
Plug-In-Gait model (*black*) and spine model (*white*)

Finally, EMG sensors will be attached to the surface electrodes. The signal-to-noise ratio will be checked to ensure clear EMG recordings.

When preparation is complete, a static calibration will be performed with the knee alignment device (KAD) to avoid knee joint angle cross-talk. Patients are asked to stand still in the middle of the force platform with arms outstretched and thumbs facing down. The KAD will be placed at the rotation axis of the knee. To ensure minimal cross-talk the KAD will be replaced three times by two different investigators. During analysis the most optimal placement of the KAD will be chosen to analyze the dynamic walking trials. Subsequently, the patients will have to walk barefoot at their natural, self-selected speed and without walking aid or orthosis, if possible, over a 12-m walkway and supervised by a skilled physiotherapist in order to avoid falls or other problems. To ensure the patient’s safety during walking, a safety harness can be worn which will not limit trunk movement. In total, a minimum of six walking trials will be recorded. Of these six trials, three will consist of clean heel strikes onto the force platforms from the right stride and three from the left so that kinetic parameters can be analyzed.

#### Allocation

A blinded investigator will allocate patients to the control or the experimental group by means of concealed envelopes which will be kept off site.

#### Interventions

All patients will receive a multidisciplinary standard care stroke rehabilitation program provided by the rehabilitation staff of RevArte. The standard care program will be patient-specific and consists of 1 h of physiotherapy and 1 h of occupational therapy. Standard care will mainly consist of gait rehabilitation, muscle strengthening and activities to enhance motor control of the arms, legs, and trunk by applying appropriate motor relearning strategies. Additionally, all patients will be receiving 30 min of speech therapy and neuropsychological treatment when necessary. Thirty participants will be assigned to the exercise group focusing on trunk coordination, selectivity, and strengthening. In total, 30 patients will be distributed to the control group. The amount of additional therapy is based on results from a meta-analysis, where at least 16 h of augmented therapy is needed within the first 6 months after stroke to achieve a favorable effect on the activities of daily living (ADL) [30]. Patients will receive the additional therapy over a period of 4 weeks. Kwakkel et al. (2004) hypothesized that a high dose of task-specific exercises should be applied over a short period of time. Therefore, both groups will receive an additional therapy hour a day, 4 days a week over a short period of 4 weeks. Although both groups receive the same amount of therapeutic input, the specificity of the training programs will be different.

The control group will be receiving the same amount of therapeutic input relevant for subjects with stroke but without the specific focus on the trunk. However, the trunk and lower limbs are involved in a variety of motor activities such as reaching, sitting without support, and active mobilization exercises [31, 32]. Therefore, a useful task has to be performed by the control group without incorporating the trunk or lower limbs. Since approximately 30% of patients will be cognitively impaired in the 5 years following a stroke, patients will be challenged to perform cognitive activities for the same amount of time [33]. For this, the RevArte Visual Search Test (RVST) of Lafosse et al. (2013) and the Visuospatial Neglect Test Battery (VNTB) of Vaes et al. (2015) will be executed by the patients. A thorough description of these tests can be found in Lafosse et al. (2013) and Vaes et al. (2015) [34, 35]. The tests are run on the Metrisquare DiagnoseIS software platform and are presented on a Wacom pen display with a large active screen area of 47.70 × 26.82 cm (total screen size of 56.39 × 37.34 cm), connected to a PC. The dual screen technology enables the researcher to observe and designate interim results at their own computer screen while the participant uses the pen at the display surface. During each of the 4 weeks, patients will perform both the VNTB and RVST, consisting of two 1-h sessions for each test battery. To prevent truncal activity the cognitive exercises will not incorporate activities where a large mechanical perturbation is induced as a positive correlation was shown between the amplitude of arm movement and anticipatory postural adjustments of the trunk [36]. Before and after the additional cognitive exercises, patients will describe their global fatigue on a Visual Analogue Fatigue Scale with 0 being fully awake and 10 being extremely tired.

The additional training for the experimental group will focus on increasing trunk control. The exercise program will consist of task-specific movements of the upper and lower part of the trunk both in the supine and sitting positions. However, we are well aware of the fact that several exercises focusing on trunk control also incorporate muscle activity of the lower limbs [31]. It is impossible to incorporate an efficient trunk exercise program with no involvement of the lower limbs. This will be achieved by executing exercises which will specifically focus on recruiting abdominal and back muscles during functional activities, strengthening of these muscles, and integrating the use of these core muscles into basic daily tasks [37]. Karthikbabu et al. (2011) concluded that trunk exercises performed on physio balls are more effective than those performed on plinths in improving trunk control and functional balance [38]. Therefore, we will be implementing a similar exercise program on unstable surfaces where patients will be receiving exercises for 25 min in a supine position followed by a 5-min resting period, and then a 30-min training session in a seated position (Table 1). Progression will be implemented in a standardized manner and determined by the physiotherapist based on the patient’s performance. The trunk exercises will always commence in the supine position, the physiotherapists need to take the safety of the patient into account when progressing to the sitting position. If safety is not guaranteed, exercises in supine will be repeated. Trunk exercises will be initiated with moderate assistance of the physiotherapist and gradually reduced to no assistance. As soon as possible, patients will have to execute the exercises with no contact between the feet and the ground to ensure a minimum of involvement of the lower limbs. Furthermore, intensity can be increased by implementing the following changes: (1) reducing base of support, (2) increasing the lever arm, (3) increasing limits of stability, (4) increasing the hold time, (5) increasing the number of repetitions, and (6) presence of visual feedback by executing the exercises with the eyes open or the eyes closed. In addition, patients will describe their global fatigue on a Visual Analogue Fatigue Scale, with 0 being fully awake and 10 being extremely tired, before and after the additional trunk exercise program.

**Table 1 Tab1:** Trunk exercise program

Position	Exercises on stable surface	Exercise on unstable surface
Supine (25 min)	Selective flexion/extension of the lower trunk	Selective flexion/extension of the lower trunk
	Pelvic bridging: lifting pelvis in crook lying with both feet supported	Pelvic bridging: lifting pelvis with lower limbs supported on physio ball
	Unilateral pelvic bridging: lifting pelvis in crook lying with one foot supported	Unilateral pelvic bridging: lifting pelvis with one leg supported on physio ball
	Pelvic bridging with displacements: lifting pelvis in crook lying and placing pelvis left and right of midline	Pelvic bridging with displacements: lifting pelvis with lower limbs supported on physio ball and place pelvis left and right from midline
	Lower trunk rotation: moving the lower limbs from left to right in crook lying	Lower trunk rotation: moving the lower limbs from left to right with legs supported on physio ball
	Lower trunk flexion: lifting lower limbs symmetrically to chest in crook lying	Lower trunk flexion: moving the lower limbs symmetrically to chest with lower limbs supported on physio ball
	Upper trunk flexion: lifting shoulder girdle symmetrically in crook lying	Upper trunk flexion: lifting shoulder girdle symmetrically with lower limbs supported on physio ball
	Upper trunk flexion rotation: lifting shoulder girdle asymmetrically in crook lying	Upper trunk flexion rotation: lifting shoulder girdle asymmetrically with lower limbs supported on physio ball
	Lower trunk flexion rotation: lifting lower limbs asymmetrically to chest in crook lying	Lower trunk flexion rotation: moving the lower limbs asymmetrically to chest with lower limbs supported on physio ball
Sitting(30 min)	Selective flexion/extension of the lower trunk	Selective flexion/extension of the lower trunk while seated on physio ball
	Selective lengthening and shortening of one side of the trunk	Selective lengthening and shortening of one side of the trunk while seated on physio ball
	Upper trunk lateral flexion: initiating movement from the shoulder girdle	External and internal perturbations while seated on physio ball
	Lower trunk lateral flexion: initiating movement from the pelvic girdle	Upper trunk lateral flexion: initiating movement from the shoulder girdle while seated on physio ball
	Upper trunk rotation: moving each shoulder forward and backwards	Lower trunk lateral flexion: initiating movement from the pelvic girdle while seated on physio ball
	Forward reach: reaching the arms out forwards from the trunk	Upper trunk rotation: moving each shoulder forward and backwards while seated on physio ball
	Lateral reach: 'reaching the arms out sideways from the trunk	Weight shifting while seated on physio ball
	Shuffling forward and backward on hard surface	Forward reach: reaching the arms out forwards from the trunk while seated on physio ball
		Lateral reach: reaching the arms out sideways from the trunk while seated on physio ball

#### Post-treatment assessment and follow-up

Immediately after the intervention and 1 month post intervention, patients will again be subjected to a clinical and biomechanical assessment to examine treatment effect and the treatment effect sustainability.

#### Discontinuations

Patients who withdraw from the study prior to intervention and after giving consent will be reported as “did not receive intervention.” If they withdraw during the 4-week intervention phase, an intention-to-threat analysis will be performed. Analysis will be performed as if the subject received the treatment (or control condition). Reasons for withdrawal will be noted.

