## Methods and design

### Study design and setting

The design of this study is a 4-week, assessor-blinded randomized controlled trial with a 1-month follow-up at an established rehabilitation hospital. Participants will be randomly allocated to either the experimental or the control group by simple randomization executed by an independent researcher who is not involved in the assessment or treatment of the patients. After participants agree to participate in this study, the independent researcher will draw one of the 60 envelopes (30 for each group) and will assign the participants to the allocated group. Patients will be recruited from the stroke population of the rehabilitation hospital RevArte, located in Edegem (Antwerp, Belgium). This rehabilitation hospital is a 194-bed facility and is able to offer inpatient and outpatient rehabilitation for approximately 300 patients at the same time. All participants will receive 16 h of either trunk or cognitive exercises in addition to the multidisciplinary standard care stroke rehabilitation program provided by the rehabilitation staff.

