### Sample size

Analysis was based on results of a previous randomized controlled trial concerning the effect of additional trunk exercises on the TT and TIS that was carried out by our research group [7]. Saeys et al. (2012) [7] reported a change score of the TT of 13.45 and 5.2 points for the experimental and control groups, respectively. The number of patients required for this study was calculated a priori to ensure sufficient statistical power. Analysis showed that a sample size of 30 patients in each group, 60 in total, was necessary to detect a difference with 80% using a two-tailed hypothesis (with significance level of *p* = 0.05).

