### Statistical analysis

Descriptive data analysis will be performed for the collected variables of the participants. The Kolmogorov-Smirnov Test and visual inspection of the data will be performed to evaluate whether the data are normally distributed. Differences between the experimental and control groups for the clinical data will be evaluated by means of repeated measures (ANOVA). Level of significance will be set at *p* < 0.05. When the stroke population is too heterogeneous, stratified sampling will be done to divide the study population into more homogenous groups. Differences along the entire kinematic, kinetics, and EMG curves will be assessed by means of spm1d in MATLAB®. Statistical parametric mapping will make interference about the topological features of statistical processes that are continuous functions [44].

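### Intention-to-treat is tied to when a patient withdraws, not to all randomised patients, and the named repeated-measures ANOVA does not by itself deliver it when scores are missing

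*Protocol article*

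**What the plan says.** Two rules stand in the protocol article under Discontinuations.

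- Before treatment: "Patients who withdraw from the study prior to intervention and after giving consent will be reported as “did not receive intervention".
- During treatment: "If they withdraw during the 4-week intervention phase, an intention-to-threat analysis will be performed" (read here as intention-to-treat). The section then adds: "Analysis will be performed as if the subject received the treatment (or control condition".

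Study design and setting gives the time of allocation: "After participants agree to participate in this study, the independent researcher will draw one of the 60 envelopes (30 for each group". Recruitment and selection places the eligibility screening with the TIS and FAC after signed consent.

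Post-treatment assessment and follow-up sets two visits after baseline: "Immediately after the intervention and 1 month post intervention, patients will again be subjected to a clinical and biomechanical assessment". Table 2 lists the Tinetti Test (TT), the primary outcome, at all three time points. Statistical analysis names the method: "Differences between the experimental and control groups for the clinical data will be evaluated by means of repeated measures (ANOVA". It does not say how a patient with a missing visit enters that analysis.

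**The concern.** Intention-to-treat describes an analysis set: everyone randomised, in the arm allocated. Here it is written as a remedy that applies if a patient leaves in one particular period. A plan that follows this text has a rule for withdrawal during treatment, a different and unclear rule for randomised patients who never start, and none for later withdrawal.

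The 1-month visit carries the second objective, whether effects last, and Data collection and management expects that some patients will have been discharged by then. Loss at that visit is therefore foreseeable.

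The method raises a second problem. If incomplete patients fall out of the ANOVA, the comparison is no longer between the groups as randomised. The Blinding section expects that patients will not stay blind, and the two additional programmes differ greatly (trunk exercise on unstable surfaces against cognitive tests on a screen). Dropout that depends on arm is plausible, though the documents give no data on it.

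**Working it through.** **Coverage of the two rules**

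| Patient leaves | Rule in the article | Status in the analysis |
|---|---|---|
| After consent, not yet randomised | Reported as untreated | Not part of a randomised comparison |
| After drawing an envelope, before treatment | Same rule | Not stated |
| During the 4 weeks | Intention-to-treat, as if treated | Arm fixed, source of missing scores not given |
| Between week 4 and the 1-month visit | None | Not stated |

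The first two rows share one rule because its window opens at consent, while both the screening and the envelope draw come after consent. The rule does not separate screening failures from randomised non-starters. There are 60 envelopes, and Sample size calls for 60 patients, so a non-starter who has drawn an envelope uses up one of the planned 60.

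**Rule against method**

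The first rule concerns patients who withdraw from the study, and the second continues with the same subject. On that reading, later scores will usually be missing. Conventional repeated-measures ANOVA over three time points needs all three values per patient. As a check, one standard implementation, given 60 simulated patients of whom 6 lacked the last visit, refused the data as unbalanced. Unless scores are filled in or another model is used, a patient with valid baseline and post-treatment TT scores contributes nothing to a three-visit ANOVA.

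**Illustration of size**

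Inputs from Sample size: TT changes of 13.45 and 5.2, 30 per group, 80% power, two-sided 0.05. Assumed, because not stated: the SD of the change and the dropout.

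1. Difference: 13.45 − 5.2 = 8.25 points.
2. The plan's 30 per group cannot be reproduced without an SD, so the SD is back-solved. Normal approximation: d = (1.960 + 0.842) × √(2/30) = 0.723, SD = 8.25/0.723 ≈ 11.4. Two-sample t test: d = 0.736, SD ≈ 11.2.
3. For comparison, SD 10 gives d = 8.25/10 = 0.825.
4. Complete cases per arm: n = 30 × (1 − loss). Power is from the two-sample comparison at that n.

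| Loss | n per arm | Power, back-solved d (normal / t) | Power, SD 10 (t) |
|---|---|---|---|
| 0% | 30 | 80% / 80% | 88% |
| 5% | 28.5 | 78.0% / 77.9% | 86% |
| 10% | 27 | 75.7% / 75.6% | 85% (84.5%) |
| 19% | 24.3 | 71.3% / 70.9% | 80% |
| 20% | 24 | 70.7% / 70.4% | 80% |
| 30% | 21 | 65.0% / 64.3% | 74% |

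5. The 19% row corresponds to 10% lost by the post-treatment visit and 10% of the remainder by 1 month: 30 × 0.9 × 0.9 = 24.3 per arm, or 48.6 of 60 with all three visits. A model that uses every available visit keeps 27 per arm at the post-treatment visit. With the back-solved effect that is 75.6% instead of 70.9%, a gain of about 5 percentage points.

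**The case against.** Three stronger readings are tempting, and the documents support none of them.

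- *Non-starters are excluded.* The article says only that they will be reported as untreated. That is a label, and no sentence removes them from the analysis. For patients who consented but were never randomised, the label is apt.
- *The protocol deletes incomplete patients.* It names repeated-measures ANOVA and no more. Deletion is how the conventional method works. Imputation or a separate baseline-to-post comparison would avoid it, and the text does not commit to one three-visit model.
- *The result will be a completers' analysis.* This goes against the stated intention to keep patients who withdraw during treatment in their arm.

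It can also be said that handling of missing data is usually left to the analysis plan, which is not shown, and that the article provides for contacting discharged patients for follow-up. The first of these stands, so silence on imputation is not the point here. The second helps retention but says nothing on patients who withdraw. Neither repairs what the article does state: an intention-to-treat rule limited to one window, and a method that does not supply what that rule needs.

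The objection to the power figures also stands. The back-solved effect size is circular, and a fall from 80% to about 70% is one scenario only.

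**Conclusion.** The concern holds in limited form. Intention-to-treat is fixed by time of withdrawal instead of by randomisation, the status of randomised non-starters is unclear, and withdrawal after week 4 falls under neither rule. The rule and the named method do not together deliver the stated analysis. With missing scores, repeated-measures ANOVA defaults to complete cases unless something else is done.

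The power loss depends on assumptions. If the SD is about 11.2 to 11.4, complete-case loss of 5% to 30% takes power from 80% to about 78% to 65% (64% by t test at the lower end). With a smaller SD the trial has room to spare. Possible bias from arm-dependent dropout matters more than power, but cannot be sized from the documents. This should be changed; it is not fatal to the design.

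**What to change.** - State that all randomised patients are analysed in their allocated arm, including those who never start and those who withdraw after week 4.
- Count consented patients who were never randomised separately, as screening failures.
- Seek the post-treatment and 1-month assessments from patients who stop the additional therapy, where they agree.
- Analyse the TT with a likelihood-based mixed model that includes baseline and uses every available visit, in place of repeated-measures ANOVA. It is valid when missingness depends only on observed data.
- Optional: a sensitivity analysis that imputes missing experimental-arm scores from the control arm.

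The cost is about two paragraphs of wording, some effort to retain patients and a little more analysis. Including non-starters may dilute the estimated effect slightly.
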